The Breteau index (BI) was on average 2 per 100 houses in 2009. With the interventions, we aim to decrease the BI with 50% to 1/100 houses. Based on the Hayes and Bennett sample size estimation (Hayes & Bennett 1999), using an inter-cluster variation coefficient of 0.5, we need a minimum of 20 clusters of 250 houses in each arm to demonstrate the effect of the ITC or PFS intervention in comparison to the control arm. We increased the number of clusters with 5% and hence will have a final sample size of 21 clusters of 250 houses/study arm. Totaling 63 clusters of on average 250 houses for the entire study.

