## *IV. C. Data collection and analysis*

Effect measures:

Primary outcomes:

Effectiveness: Breteau Index, House index, Pupae per person index, (adult mosquito infestation)

confirmed Dengue cases (if any). Comparison of infestation at each time point between the intervention arms, taking into account the pre-intervention infestation levels and the cluster design. Generalized linear random effect regression models with a negative binomial link function will be used.

Secondary output:

Uptake and use of ITC

Acceptance of PFS and ITC (and identification of underlying lay dimensions of acceptability)

Change in intra-and extradomiciliary risks for Aedes infestation

Cost- effectiveness of ITC and of PFS

Residual insecticidal activity of deltamethrin applied in ITC and in PFS

Data collection:

1. Baseline study (in both intervention and control arms) :
   1. Entomological survey:

Existing of larval and pupal surveys; the larval surveys will be conducted as in the routine system (exhaustive inspection of all houses and potential water holding containers on the presence of immature stages of Aedes). The traditional Stegomyia indices will be calculated: the House Index (HI) and Breteau index (BI). Collection of adult mosquitoes: during routine surveys, the vector control teams are also inspecting houses in the search of adult mosquitoes.

The pupal surveys will consist of direct inspection of potential water-holding containers inside and around the houses following the recommendations of Focks (Focks 2004). This will be done by a special team in 20% of the house-blocks (randomly chosen: 23 houseblocks/arm). All containers where immature stages of Aedes are detected will be emptied and the absolute number of pupae will be counted. For elevated water tanks a sweeping method will be used to collect the majority of the pupae. The total number of positive containers for Ae. aegypti pupae and their relative contribution to total pupal production will be recorded and computed. The number of persons per house will be also enquired (during the distribution of tools) for the construction of Pupal Index per inhabitant (PPI) at the cluster level.

- 1. Evaluation of main intra and extra domiciliary risks at household and environmental risks at community level in each houseblock included in the study: data collected by the routine vector control programme teams through observation, guided by an observation guide (Annex 5).

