We will collect during the assay the financial cost of the routine vertical programme and will calculate the average cost per house inspected and treated.

For each arm, we will multiply the number of houses inspected and treated annually during the study by the corresponding average cost described above, to calculate the total annual cost of the routine programme per arm.

We will calculate the total economic cost of the new control tools (ITC and PFS): The economic cost of the community participating in the set up, the financial and economic cost of the routine programme during set up, distribution, installation and maintenance of the tools; and the economic cost of the community participating in collective vector control activities.

The total annual cost of the different arms can be obtained adding the cost of the routine programme and the economic cost of the implemented strategy.

We also will calculate the average and marginal cost per house within arms and incremental cost per house between arms.

The activities of vertical programme will be costed prospectively every month during two years of the study, as well as the cost regarding the distribution of the tools itself, every time it happens (see annex 11-12-13-14-15-16). The cost information about participation in individual and collective activities related to vector control of the community will be followed by questions included in the acceptability survey 3 times during follow up period, in 400 houses per arm for the two intervention arms and with quarterly surveys on the routine activities done (annex 8 ).

We will obtain the effectiveness measure from the entomological and epidemiological study and use the difference of differences between the baseline data and the data for the subsequent periods as effectiveness measure.

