We will calculate arithmetic means and 95% confidence intervals when making cost and effectiveness (entomological indices) comparisons between the three arms of the trial. We will carry out incremental analysis, with the mean cost difference between study’s arms divided by corresponding mean difference of entomological indices to give the incremental cost effectiveness ratio (ICER). We will use the non-parametric percentile method for calculating the confidence interval around this ratio with 1000 bootstrap estimates of the mean cost and entomological indices differences. We will carry out sensitivity analysis, varying the price of the tools, and using the variation observed in the correlation between the coverage of tools and the corresponding entomological outcome.

1. Sociological qualitative study on acceptability

In-depth interviews will be conducted in a purposive sample of 20 households where ITC have been distributed and PFS initiated. The households will be identified from data collected by the household survey and through program staff. The interviews will be conducted:

- - 1. 4 months after distribution of ITC and PFS with 10 household heads which have either 1°) not accepted the tools at the onset; 2°) accepted the tools or 3°) accepted with reluctance.
    2. 12 months after distribution of ITC and PFS with 10 household heads which have either 1°) accepted the tools, 2°) accepted with reluctance, and 3°) who have stopped to use them after a period of one year.

The sampling is tentative and could be increased depending on the results of preliminary data analysis. We will also explore the perceptions of the interviewees on the routine *Aedes* *aegypti* control strategy (topics guide and informed consent for in-depth interview: annex 17 and 18).

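### The cost-effectiveness ratio uses a differenced effect that is less precise than the planned regression adjustment, and a percentile interval that cannot be read when the effect is small

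*Protocol*

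**What the plan says.** Protocol section IV.C handles baseline infestation in two ways.

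- **Effectiveness (Primary outcomes).** Arms are compared at each time point, "taking into account the pre-intervention infestation levels and the cluster design", in random-effects regression models of negative binomial type.
- **Cost-effectiveness evaluation.** The effect is drawn from the entomological and epidemiological study, and the plan is to "use the difference of differences between the baseline data and the data for the subsequent periods as effectiveness measure". Arithmetic means are compared between the three arms, and the mean cost difference is divided by the mean index difference. For uncertainty: "We will use the non-parametric percentile method for calculating the confidence interval around this ratio with 1000 bootstrap estimates".

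The section names no resampling unit and no rule for replicates in which the index difference is zero or changes sign. The planned sensitivity analyses vary the tool price and the relation between coverage and outcome, not the method for the ratio.

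Cost-effectiveness is part of the general objective (III.A) and is specific objective 3 (III.B). Section IV.C lists it as a secondary output.

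**The concern.** **Denominator.** Subtracting the whole baseline value gives it a weight of one, however noisy it is. Regression adjustment estimates the weight. In a randomised comparison both target the same arm difference, but differencing carries all the baseline noise into the result. The Timeline gives months 1 to 3 to preparation and baseline, against monthly entomological evaluation from month 4 to month 28, so a short baseline is set against a long average. The less precise estimate would go into the cost-effectiveness ratio.

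**Interval.** A ratio has no sensible order across a zero denominator. If a tool costs more, then as its benefit shrinks towards zero the ratio rises without limit. Once the benefit turns slightly negative, the ratio jumps to a large negative value. Sorting the replicates therefore places outcomes that are dearer and worse below the most favourable ones. If the cost difference can also change sign, a negative ratio may mean either cheaper and better or dearer and worse. Percentiles of such a set are not limits for anything.

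At stake is the uncertainty statement for the cost-effectiveness objective when an effect against routine control is weak, or when the curtains (ITC) and the spraying (PFS) perform alike.

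**Working it through.** **1. The plan's own figure.** Inputs from section IV.A: "The Breteau index (BI) was on average 2 per 100 houses in 2009"; "we aim to decrease the BI with 50% to 1/100 houses"; "using an inter-cluster variation coefficient of 0.5"; 250 houses per cluster. Alpha and power are not stated; two-sided 0.05 and 80% are assumed. The Hayes-Bennett formula is

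c = 1 + (z_α/2 + z_β)² × [(λ0+λ1)/y + k²(λ0²+λ1²)] / (λ0−λ1)²

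= 1 + 7.849 × [0.03/250 + 0.25 × 0.0005] / 0.0001 = 1 + 7.849 × 2.45 = 20.23.

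This agrees with "we need a minimum of 20 clusters of 250 houses in each arm", and 20 × 1.05 = 21. The variance components below are therefore the plan's own.

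**2. Simplest case for the denominator.** With one survey before, one after, equal variances and correlation ρ, the variance ratio of differencing to regression adjustment is 2/(1+ρ): 2.00 at ρ = 0, 1.54 at 0.3, 1.33 at 0.5, 1.18 at 0.7. For ρ ≥ 0, two is the ceiling.

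**3. The planned schedule.** Assume 3 baseline surveys, 24 follow-up surveys and 21 clusters per arm. In units of index points per 100 houses:

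- Poisson variance per cluster-survey: 100 × 2/250 = 0.8 at BI 2, and 0.4 at BI 1.
- Between-cluster variance: 0.25 × 2² = 1 at BI 2, and 0.25 at BI 1.
- A share π of the between-cluster variance persists from baseline to follow-up. The rest varies independently from survey to survey.

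Write V_b for the baseline variance (the same in both arms), V_c and V_t for the control and treated follow-up variances, and C_c and C_t for the covariances with baseline. Then

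- differencing: D = 2V_b + V_c + V_t − 2C_c − 2C_t
- regression: A = V_c + V_t − (C_c + C_t)²/(2V_b)

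Example, π = 0.5 at the planned effect: V_b = 0.5 + 0.5/3 + 0.8/3 = 0.933; V_c = 0.5 + 0.5/24 + 0.8/24 = 0.554; V_t = 0.125 + 0.125/24 + 0.4/24 = 0.147; C_c = 0.5; C_t = 0.25. So D = 1.068 and A = 0.400, a ratio of 2.67. The standard errors are √(1.068/21) = 0.225 and √(0.400/21) = 0.138.

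| π | Planned effect (BI 2 vs 1): SE differenced / adjusted | Variance ratio | No effect (BI 2 vs 2): variance ratio |
|---|---|---|---|
| 1.0 | 0.199 / 0.140 | 2.02 | 1.23 |
| 0.5 | 0.225 / 0.138 | 2.67 | 1.70 |
| 0.2 | 0.240 / 0.116 | 4.31 | 2.83 |

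If the non-persistent part is instead constant within each period (V_b = 1.267, V_c = 1.033, V_t = 0.267 at the planned effect), the ratios at π = 1, 0.5 and 0.2 are 2.02, 2.16 and 2.56 at the planned effect, and 1.23, 1.56 and 1.90 at no effect. The overall range is about 1.2 to 4.3.

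**4. The ratio interval.** Take a standard error of 0.22 for the effect difference δ (within the 0.20 to 0.24 above) and an illustrative cost difference of 3 with standard error 0.3, in arbitrary units.

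| δ per 100 houses | Wrong-sign replicates, Φ(−δ/0.22) | 95% percentile limits of the ratio |
|---|---|---|
| 1 (planned) | Φ(−4.5), about 3 in a million | about 2.0 to 5.4 |
| 0.25 | Φ(−1.14) = 12.8% | about −106 to +123 |
| 0 | 50% | not interpretable |

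**5. A less favourable setting.** A simulation used one survey before and one after, true-rate correlation 0.5, clusters resampled, and an assumed cost difference of 5.7 USD per house (3 × 1.9) with standard deviation 1. The interval spanned both signs in 37% of trials at a 50% reduction, 78% at 25%, and 93% at both 10% and zero. This ignores the averaging over monthly surveys, so it is a pessimistic bound for the planned effect.

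**The case against.** **Differencing is itself a baseline adjustment, and an additive summary is needed.** This is fair. The negative binomial model naturally yields a rate ratio, while a cost-effectiveness ratio needs an absolute difference. Having a separate summary is therefore no error in itself. What stands is that an absolute difference can also be obtained with regression adjustment, and more precisely.

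**A reader might infer that differencing at least doubles the variance.** The documents do not support that. In the simplest case two is the maximum, and at no effect most of the ratios above are below two. Nor is differencing always worse than ignoring baseline. With full persistence its variance is 0.8333/1.3 = 0.64 of that from follow-up alone at the planned effect; at π = 0.5 it is 1.0677/0.701 = 1.52. The protocol gives neither the persistence nor the number of baseline surveys.

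**A reader might infer a seasonal bias**, because baseline falls outside the stated April and September peaks. Arms are randomised and surveyed in parallel, so the expected baseline difference is zero and only precision suffers.

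**A reader might infer that the bootstrap inflates the effect variance, or that the interval always fails.** It does neither. The ratio's behaviour is a separate matter, and at the planned effect with averaged surveys the limits are ordinary.

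**Objective 3 compares each tool with routine control, not ITC with PFS.** That is correct, so the case of two similar tools is not objective 3 as worded. Section IV.C does, however, announce cost and effect comparisons between all three arms.

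**This is analysis-plan detail.** Planes, curves and the resampling unit often are. But the protocol itself fixes the differenced measure and the percentile interval for the ratio, so the choice has been made here.

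**Conclusion.** Both points hold, as separate points and within limits.

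1. The differenced effect is less precise than regression adjustment in every scenario examined. The variance ratio is about 1.2 to 4.3, assuming 3 baseline and 24 follow-up surveys, a coefficient of variation of 0.5, and persistence between 20% and 100%. It is a loss of precision, not a bias.
2. The percentile interval for the ratio becomes unreadable when the effect difference is small relative to its standard error: a weak effect against control, or two tools that perform alike. At the planned 50% reduction it may well be ordinary. How often it fails there depends on how far averaging over surveys lowers the standard error.

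The cost figures are illustrative only. The point concerns a secondary output and leaves the sample size and the effectiveness analysis untouched. It is worth correcting because the cost-effectiveness objective rests on this ratio and the remedy needs no new data.

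**What to change.** In the cost-effectiveness part of section IV.C:

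- Use the baseline-adjusted arm difference, expressed on the index scale, as the denominator of the ratio.
- State that whole clusters are resampled within arm, with cost and effect kept together in each replicate.
- Report the point estimate of the ratio with the bootstrap replicates on the cost-effectiveness plane, and incremental net benefit or acceptability curves over a range of thresholds.
- Give a percentile interval for the ratio only when the effect difference does not change sign across the replicates.

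The cost is a change of wording and a little more programming. The one real drawback is that net benefit needs a value per index point. The protocol supplies none, so a range of willingness-to-pay values must be shown.

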## *IV.D. Quality Control*

1. Documentation and standardization of the different activities to be executed in the project:
   1. Standardization of training, repeated in each health area
   2. Description of process of PFS (annex 4) and of ITC implementation (annex 3)
   3. Data collection for pupal surveys
   4. Data collection for entomological surveys (existing routine system is standardized); quality control routinely done in 60% of the households
2. Data entry will be performed in Access, questionnaires already coded, a control check of 5% of the data will be done by an external independent person
3. The information given in questionnaires will be cross-checked with direct observation if indicated.

## *IV. E. Ethical concerns*

The protocol will be revised by the ethical committee of the Institute of Tropical Institute (IPK), Havana and the Cuban health authorities, by the scientific board of Institute of Tropical Medicine, Antwerp, Belgium, and the ethical committee of the University of Antwerp, Belgium.

Informed consent from local authorities and community representatives for distributing new vector control tools in the area will be obtained. Informed consent of interviewees and Focus group discussion participants will be taken. The researcher will explain the research project: the objectives, the funding, methods, the involvement of the participants and the length of time of involvement, and plan on the use of the research outcomes, including how these will be disseminated. All this information will be placed in the written Informed Consent form for the ITC areas (annex 1).

For the houses included in the PFS arm, no special informed consent form was designed (as residual spraying is not a new activity and has already been implemented by the routine programme), the signature of informed consent will be obtained on the form filled in by the health worker during application.

The confidentiality of data will be ensured during data management and analysis. Participants will not be identified in any written or oral report, especially in relation to the data they provided.

**Critical assessment and possible limitation of the study design and methodology in relation to project objectives:**

The main limitation is the use of the routine entomological information to compare the effectiveness between study groups: this data collection has standardized procedures. However different vector control technicians are collecting it and few data can be (randomly) missing. We will improve the quality assurance system in place to secure validity of the measurement of entomological variables.

## Timeline

|  | Year 1 |  |  |  |  |  |  |  |  |  |  |  | Year 2 |  |  |  |  |  |  |  |  |  |  |  | Year 3 |  |  |  |  |  |
| --- | --- | --- | --- | --- | --- | --- | --- | --- | --- | --- | --- | --- | --- | --- | --- | --- | --- | --- | --- | --- | --- | --- | --- | --- | --- | --- | --- | --- | --- | --- |
|  | 1 | 2 | 3 | 4 | 5 | 6 | 7 | 8 | 9 | 10 | 11 | 12 | 1 | 2 | 3 | 4 | 5 | 6 | 7 | 8 | 9 | 10 | 11 | 12 | 1 | 2 | 3 | 4 | 5 | 6 |
| Preparation and baseline | X | X | X |  |  |  |  |  |  |  |  |  |  |  |  |  |  |  |  |  |  |  |  |  |  |  |  |  |  |  |
| Distribution of curtains |  |  |  | X |  |  |  |  |  |  |  |  |  |  |  |  |  |  |  |  |  |  |  |  |  |  |  |  |  |  |
| Perifocal spraying |  |  |  | X |  |  |  |  | X |  |  |  | X |  |  |  | X |  |  |  | X |  |  |  | X |  |  |  |  |  |
| Entomological evaluation |  |  |  | X | X | X | X | X | X | X | X | X | X | X | X | X | X | X | X | X | X | X | X | X | X | X | X | X |  |  |
| Pupal surveys |  |  |  | X |  |  |  |  | X |  |  |  |  |  |  | X |  |  |  |  | X |  |  |  |  |  |  | X |  |  |
| Acceptance evaluation |  |  |  |  |  |  |  |  | X |  |  |  |  |  |  | X |  |  |  |  |  |  |  |  |  |  |  | X |  |  |
| ITC Use survey |  |  |  |  |  |  |  |  |  |  |  |  | X |  |  |  |  |  |  |  | X |  |  |  | X |  |  |  |  |  |
| Environmental risks |  |  | X |  |  |  |  |  |  |  |  |  |  |  | X |  |  |  |  |  |  |  |  |  |  |  | X |  |  |  |
| Registration VC activities |  |  |  |  |  | X |  |  |  | X |  |  |  | X |  |  |  | X |  |  |  | X |  |  |  | X |  |  |  |  |
| Residual activity testing ITC |  |  |  | X |  |  |  |  |  | X |  |  |  |  |  | X |  |  |  |  |  | X |  |  |  |  |  | X |  |  |
| Residual activity testing PFS |  |  |  | X | X | X | X |  |  |  |  |  |  |  |  |  |  |  |  |  | X | X | X | X |  |  |  |  |  |  |
| Susceptibility testing |  |  |  |  |  |  | X | X | X |  |  |  |  |  |  |  |  |  | X | X | X |  |  |  |  |  |  |  | X | X |
| Economic evaluation |  |  |  | X | X | X | X | X | X | X | X | X | X | X | X | X | X | X | X | X | X | X | X | X | X | X | X | X |  |  |
| Analysis and report writing |  |  |  |  |  |  |  |  |  |  |  |  |  |  |  |  | X |  |  |  |  |  |  |  |  |  |  | X | X | X |

Reference List

